## 9 SELECTION AND WITHDRAWAL OF PARTICIPANTS

### 9.1 Inclusion criteria

To be included in the trial the participant must:

- Have given written informed consent to participate
- Age 16 years or older at the time of consent
- Have confirmed NS at Day 0 (Start of Protocolised Prednisolone regimen (SPPR)) (defined as serum albumin < 35g/l and PCR>300mg/mmol) secondary to MCD/FSGS with,
  - *De novo* disease, or;
  - Relapsing disease in a patient previously steroid or CNI responsive (this is defined as patients who have achieved complete or partial remission from their NS in response to treatment with steroid or CNI).
- Biopsy proven MCD or FSGS (from medical records)
- Agreed to be enrolled in the National Registry of Rare Renal Diseases (RaDaR)

### 9.2 Exclusion criteria

The presence of any of the following will preclude participant inclusion:

- MCD or FSGS due to secondary causes, including obesity-driven hyperfiltration, remnant kidneys, malignancy of a type likely to be associated with MCD /FSGS and genetic polymorphisms known to be associated with nephrosis
- MCD/FSGS secondary to malignancy, including lymphoproliferative disorders
- Family history of MCD or FSGS in a first degree relative unless previously shown to be steroid responsive
- Previous rituximab within 18 months preceding Day 0 (SPPR), or 12 months if there is evidence of B cell return in peripheral lymphocyte subsets
- Previous cyclophosphamide within 6 months preceding Day 0 (SPPR)
- Prednisolone daily dose equal to or greater than 60mg, with a course length of greater than 4 weeks, immediately prior to randomisation
- Evidence of current or past infection with Hepatitis B, C or HIV (unless appropriate prophylaxis is given and no replicating virus is detected).
- Positive serum pregnancy test (within 14 days prior to treatment with IMP in main trial and rituximab in OLP)
- Evidence of active severe infection
- Severe heart failure or severe, uncontrolled cardiac disease
- Pregnant or breast-feeding women
- Live vaccine administration in the four weeks prior to enrolment and while remaining on IMP treatment
- Previous/known hypersensitivity to prednisolone or IMP or to murine proteins (and any excipients as described in section 6.1 of the SmPC).
- Co-enrolment in another clinical trial of an investigational medicinal product
- Any other reason which, in the opinion of the Principal Investigator (PI), renders the patient unsuitable for the trial.

### 9.3 Treatment assignment and randomisation number

#### 9.3.1 Method of randomisation

Eligible participants will be randomly assigned to either the standard of care + placebo

(control arm) or the standard of care + rituximab (research arm) in a 1:1 ratio using the stratified random block method. Stratification factors are:

- Patient type
- Disease type
- Prednisolone regimen

### 9.3.2 Procedure of randomisation

A web-based central randomisation system will allocate each participant a Trial Subject ID and treatment kit code.

At site initiation meetings, the trial co-ordinator will arrange for the suitably trained and delegated members of trial team to have access to a unique system username and password, which will allow them to access the central randomisation system. The trial co-ordinator will also train site staff in how to access and use the randomisation system throughout the trial.

In order to enrol a patient, data will be entered onto the central randomisation system via an internet-based interface. The following data will be required in order to randomise a patient:

- Confirmation that the patient satisfies all the eligibility criteria
- Patient's date of birth
- Patient type (*De novo* disease vs. relapsing disease)
- Disease type (MCD vs. FSGS)
- Prednisolone regime (Regimen 1 vs Regimen 2)

A unique treatment kit code will be allocated and a unique trial Subject ID will be assigned by the randomisation system for the participant. The treatment kit code will be used by the unblinded pharmacy or other authorised site personnel to determine the treatment arm the participant has been randomised to.

A paper-based randomisation system will also be in place as a back-up if the online randomisation system is unavailable. See section 9.3.2.1 for further details.

#### 9.3.2.1 Paper randomisation

If the web-based randomisation system is unavailable to randomise an eligible participant at any participating site, the site team can contact the trial coordinators based in Cambridge to request paper randomisation be carried out.

In order to randomise a participant, the following data will be required:

- Confirmation that the patient satisfies all the eligibility criteria
- Patient's date of birth
- Patient type (*De novo* disease vs. relapsing disease)
- Disease type (MCD vs. FSGS)
- Prednisolone regime (Regimen 1 vs Regimen 2)

A unique treatment kit code will be allocated and a unique trial Subject ID will be assigned by the trial coordinator via paper-based randomisation system. The email containing details of Subject ID, kitcode and site details will be sent to site team, site pharmacy, CI and co-lead.

The treatment kit code will be used by the unblinded pharmacy or other authorised site personnel to determine the treatment arm the participant has been randomised to.

The data used to randomise participants by this method will be retrospectively added onto the web-based system when it is available again by authorised delegated individuals and site teams will be made aware they can access this data via the web.

#### 9.4 Method of blinding

During the double-blind phase of the trial, participants and research teams (excluding the site pharmacy or other authorised site personnel) will be blinded to the treatment group until participants reach the primary end point of relapse or end of trial. At the point of relapse, participants and the local Principal Investigator will be unblinded to assess whether they are eligible to progress into the Open Label Phase. If the trial is stopped earlier (e.g. for safety reasons), at the recommendation of the Independent DMC and the approval of the TSC, all participants would be unblinded. Unblinding could also occur at the request of the local investigator if participants have failed to achieve at least partial remission at 16 weeks, and if unblinding is necessary for patient safety when further treatment decisions are made. The physical appearance of the IMPs is matched and the IMPs will be presented in identical packaging at the point of release by site pharmacies.

#### 9.5 Participant Withdrawal Criteria

Participants who are withdrawn or choose to withdraw from the trial will not be replaced.

##### 9.5.1 *Withdrawal from protocol treatment*

A participant may withdraw, or be withdrawn, from the trial treatment for the following reasons:

- Participants who do not achieve partial remission by 16 weeks after Day 0 (SPPR). The treating clinician may request unblinding of withdrawn participants if required for safety consideration of future treatment – this unblinding will be performed at local site level only
- Participants who enter the trial and remit and relapse before receiving the first dose of trial IMP. In this case the participant can be withdrawn from the trial and re-screened as a new participant. It is recommended the clinician chooses Regimen 1 steroid taper for this participant when re-entering them into the trial
- Progressed or relapsed disease whilst on therapy
- Unacceptable toxicity
- Participant choice
- Addition of other immunosuppressants for treatment of MCD/FSGS
- Any alterations in the participant's condition which justifies the discontinuation of treatment in the investigator's opinion.
- Failure to adhere to infusion visit schedule. With ongoing consent, patients should remain in the trial and be followed up according to the protocol visit schedules. Samples and data collected up to the time of withdrawal will be included in the data reported for the trial.

### 9.5.2 *Duration of safety reporting*

Safety reporting of SARs/SUSARs is required for trial participants withdrawn from trial treatment (including those withdrawn from trial treatment eg for non-response) for a minimum of 12 months following the last dose of IMP. Rituximab causes B cell depletion, with B cell recovery beginning within 6 months. By 12 months after treatment, B cell counts have generally returned to normal (Truxima SmPC).

If a trial participant has withdrawn his/her consent all trial-specific tests and assessments should be stopped from the point of withdrawal, including safety reporting.

They should be followed up by their treating clinicians until the event resolution but no new data should be collected from them for the trial purposes

### 9.5.3 *Withdrawal of consent*

Patients may withdraw their consent to participate in the trial at any time. If the patient explicitly states their wish not to contribute further data to the trial, the investigator should inform the co-ordinating centre in writing and the withdrawal of consent should be documented by the investigator in the patient's case report forms (CRF). However, data collected up to the time of consent withdrawal will be included in the data reported for the trial.

## 10 TRIAL TREATMENT

### 10.1 **Treatment summary**

For the purpose of this trial, the following are considered as IMPs:

#### *Double-blind phase*

- Rituximab
- Placebo to match Rituximab (sodium chloride 0.9%)

#### *Open label phase*

- Rituximab

#### 10.1.1 *Supply*

All IMPs and Non-IMPs in this trial will utilize standard commercial stock. Biosimilar rituximab preparations are permitted.

#### 10.1.2 *Name and description of Rituximab*

Rituximab is a monoclonal antibody that targets CD20, a protein found on the surface of B lymphocytes. Once rituximab has bound CD20, it causes depletion of B cells circulating in the blood by three mechanisms:

- Antibody dependent cellular cytotoxicity
- Complement dependent cytotoxicity
- Apoptosis

Rituximab was approved for medical use in 1997. It is on the World Health Organisation's List of Essential Medicines, the most important medications needed in a basic health care system. It is licensed for use in refractory rheumatoid arthritis in both USA and Europe with extensive RCT and registry data supporting its efficacy and safety. There are also data

supporting the use of rituximab to treat other autoimmune diseases affecting the kidneys including lupus nephritis and ANCA associated vasculitis (AAV). NHS England currently fund rituximab treatment for patients with refractory systemic lupus erythematosus (SLE) and AAV, hence the UK nephrologists are familiar with using the drug. In these diseases, rituximab is given as 2 doses of 1g two weeks apart inducing B cell depletion for 6-12 months. Rituximab is also being used as a maintenance agent, with repeat dosing every 6 months shown to be safe and effective.

#### 10.1.3 Legal status

Rituximab is licensed for the treatment of a number of conditions, including B cell lymphoma, Rheumatoid Arthritis and ANCA Vasculitis. It has previously been studied in paediatric populations. Within this trial, the IMP is being used in a new population (adults with de novo or relapsing nephrotic syndrome secondary to MCD/FSGS).

The trial is being carried out under a Clinical Trial Authorisation. The drug is therefore only to be used by the named investigators, for the participants specified in this protocol, and within the trial.

#### 10.1.4 Packing and labelling

IMP infusions will be supplied with a blinded label at the point of dispensing.

#### 10.1.5 Storage conditions

Rituximab will be stored in accordance with the requirement of its respective SmPC.

#### 10.1.6 Maximum duration of treatment of a participant

Patients will receive rituximab treatment at the start of the trial for up to 26 (+/- 2) weeks from Day 0 (SPPR). Those patients in the control arm who consent to the Open Label Phase of the trial will receive treatment with the intervention described for the rituximab arm in the main trial – i.e. for a further 26 (+/- 2) weeks.

#### 10.1.7 Dose

The rituximab dose used is 1g for all treatments. Rituximab 1g will be administered within 4 weeks of Day 0 (SPPR) and is then repeated after 2 weeks (- 1 week or + 2 weeks). Provided the participant achieves partial or complete remission by week 16, a further 1g is administered at 26 weeks (+/- 2 weeks) from Day 0 (SPPR).

#### 10.1.8 Administration

Rituximab will be administered intravenously as per SmPC instructions. To reduce the risk of infusion reactions, pre-medication will be given prior to each dose as per local practice – the recommended regime is methylprednisolone 100mg intravenously, chlorpheniramine 10mg intravenously and paracetamol 1g orally.

#### 10.1.9 Known drug reactions

Known drug reactions for rituximab are summarised in Section 4.8 of the SmPC for Rituximab approved by the Medicines and Healthcare products Regulatory Agency (MHRA) for use in this trial. Currently, there is limited data on possible drug interactions with Rituximab.

#### 10.1.10 Dose modifications

Dose modifications to IMP treatment are not permitted. Treatment with rituximab will not

proceed if a participant suffers an Adverse Reaction to the drug (at the discretion of the treating clinician).

#### **10.1.11 Placebo**

Patients randomised to placebo will receive a NaCl 0.9% infusion to match the rituximab infusion, administered at the same time points and prepared by unblinded site pharmacy or other authorised site personnel. Patients in the placebo arm will also receive pre-medication as per local practice, the recommended regime is methylprednisolone 100mg intravenously, chlorpheniramine 10mg intravenously and paracetamol 1g orally.

### **10.2 Open Label Phase (OLP)**

Patients randomised to placebo who achieve partial/complete remission by week 16, followed by disease relapse (the primary endpoint event) within 24 months of Day 0 (SPPR) will be invited to participate in the Open Label Phase (OLP) of the trial.

Participants who fail to remit by week 16 will be ineligible for the OLP, as patients who are not steroid responsive are unlikely to respond to rituximab therapy. There is limited data in this group, but a single open label RCT in children whose nephrotic syndrome was unresponsive to steroids and CNIs did not show any benefit of rituximab. Data arising from the OLP will not contribute to either the efficacy or safety assessments in the main phase of the trial but will allow exploratory observational analyses, including a comparison of time in remission combining both standard of care or placebo treatment and rituximab treatment.

Those participants in the control arm who consent to the OLP will receive treatment with the intervention described for the rituximab arm in the main trial – i.e. receive rituximab 1g within 4 weeks of relapse and restarting treatment prednisolone, after 2 weeks (+/-7 days) and, if they continue in remission, after 26 weeks (+/- 2 weeks) of restarting treatment dose prednisolone for relapse. Thus participants will attend 3 additional visits on top of standard care for the rituximab infusions. SAE reviews and concomitant medication reviews will be conducted during these visits.

All participants that enter the OLP will recommence protocolised prednisolone therapy as in the main trial (with the regimen at the discretion of the local investigator).

### **10.3 Non IMPs**

#### **10.3.1 Prednisolone**

Prednisolone is a glucocorticoid used very widely used to treat a multitude of conditions. Side effects are also well described, including increased risk of infection and diabetes, osteoporosis, weight gain, fluid and salt retention, gastritis, skin thinning, poor wound healing, weight gain and a moon face.

In the trial, patients will be prescribed daily oral prednisolone to take at home on a reducing schedule according to the trial protocol. The Protocolised Prednisolone Regimen (PPR) will be started at Day 0, which may be combined with the screening visit if it is clinically appropriate to start glucocorticoid therapy at this time point.

Prednisolone will be dosed as follows:

**REGIMEN 1:** is based on National and International guidelines for the treatment of nephrotic FSGS. Prednisolone 1mg/kg/day (max 60mg) started (or continued) at Day 0, and continued daily for up to 16 weeks. A maximum of two weeks after obtaining partial or complete remission of proteinuria the prednisolone dose will be reduced to:

40mg daily for 2 weeks  
30mg daily for 2 weeks  
25mg daily for 2 weeks  
20mg daily for 2 weeks  
15mg daily for 2 weeks  
10mg daily for 2 weeks

Thereafter, reduction will be 5mg daily for 2 weeks, 5mg alternate days for 2 weeks then stop or reduction to a maintenance dose of <10mg daily for patients on long term prednisolone (with further reduction determined by the local investigator as clinically appropriate). This regimen is recommended for patients with a first presentation of the nephrotic syndrome.

**REGIMEN 2:** In patients at risk of steroid toxicity or who have previously responded rapidly to prednisolone, local investigators can choose a lower dose regime. Patients will start treatment with prednisolone 1mg/kg/day (max 60mg) continued daily for up to 16 weeks, and a maximum of two weeks after obtaining partial or complete remission of proteinuria will reduce the dose to:

30mg daily for 2 weeks  
20mg daily for 2 weeks  
15mg daily for 2 weeks  
10mg daily for 2 weeks

Thereafter, reduction will be 5mg daily for 2 weeks, 5mg alternate days for 2 weeks then stop or reduction to a maintenance dose of <10mg daily for patients on long term prednisolone (with further reduction determined by the local investigator as clinically appropriate).

Local investigators will select the appropriate prednisolone regime prior to randomisation based on previous toxicity and steroid responsiveness. The regimen selection will be stratified at randomisation. Variations in prednisolone doses of up to one third of the selected regime will be permitted and will not be considered protocol violations. However, any increase in prednisolone dose should be discussed with the trial management team before being prescribed.

Tapering steroid diaries will be provided for participant's use - completion of these is not mandatory. The diaries should be reviewed at trial visits to aid CRF completion.

#### 10.3.2 Calcineurin inhibitors (CNIs)

Tacrolimus and cyclosporine are immunosuppressive medications widely used after organ transplantation. They are also used to treat primary glomerulonephritis, and patients with SD/FR MCD/FSGS are often treated with these drugs. These drugs will be permitted in patients enrolled into the trial.

Following randomisation, the daily CNI dose will be reduced as follows:

25% dose reduction within 48 hours of randomisation

50% dose reduction (from dose at randomisation) at week 4 (+/-2 weeks) (from Day 0 SPPR)

75% dose reduction (from dose at randomisation) at week 8 (+/-2 weeks) from Day 0 SPPR)

The CNI will then be stopped at week 12 (+/-2 weeks) from Day 0 SPPR.

Variations in the daily CNI dose of up to 25% at each of these time points will be permitted and will not be considered protocol violations.

[figure not shown]

### 10.3.3 Concomitant therapy

Participants will continue to be treated with routine concomitant medications for other co-morbidities as appropriate within their current clinical condition, with modifications e.g. oral to IV switches, or temporary cessation as necessary. Appropriate supportive care may also be prescribed, including fluids, nutritional supplements and other medications as necessary. Other immune suppression for NS (excluding prednisolone and CNIs), e.g. mycophenolate mofetil will be stopped at randomisation.

All concomitant medications will be reviewed by local direct care team as per preferred local practice but only specified concomitant medications detailed below will be recorded in the CRF.

Prophylaxis against *Pneumocystis Jiroveci* pneumonia should be given for at least 6 months from starting trial treatment, as per local practice. It is recommended that blood pressure should be controlled to a target of < 130/80mm Hg. The use of Angiotensin Converting Enzyme inhibitors (ACEi) and Angiotensin Receptor Blockers (ARB) at the highest dose tolerated is strongly recommended and the use will be recorded.

Prophylaxis against glucocorticoid induced peptic ulceration and osteoporosis is also recommended as per local practice. Consideration should be given to performing a bone density assessment at the start of the trial and at six months to assess glucocorticoid induced bone loss.

Prophylaxis against venous thromboembolic disease is recommended in patients with serum albumin below 20g/l as per local practice.

Prophylaxis against tuberculosis is also recommended in high risk patients according to local practice.

The use of live viral vaccines during IMP treatment or while remaining B-cell depleted is not advised; should any vaccines be required during the study, it is recommended these should be completed at least 4 weeks prior to commencing the next dose of IMP.

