| Comparator product                                                                                                     | Placebo                                                                                                                                                                                                                                                                                                                                                                                                                                      |
| nIMPs                                                                                                                  | Prednisolone and CNIs                                                                                                                                                                                                                                                                                                                                                                                                                        |
| Route(s) of administration                                                                                             | IV                                                                                                                                                                                                                                                                                                                                                                                                                                           |
| Maximum duration of treatment of a participant                                                                         | Main study phase: 26 weeks
Open Label Phase: additional 26 weeks post relapse                                                                                                                                                                                                                                                                                                                                                             |

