| Additional Health Costs questionnaire                               |   | x |  |                                                                                                                                                                                                                                                               |   | x |   | x |   | x | x  | x | x | x | x |
| IMP administration                                                  |   |   |  | ≤4 weeks after SPPR (dose 1), repeated 2 weeks later (- 1 week or + 2 weeks allowed)(dose 2), and in week 26 (+/- 2 weeks) (dose 3) if remission by week 16 achieved and maintained. The week 24 visit could be combined with the week 26 IMP administration. |   |   |   |   |   |   |                 |   |   |   |   |
| Prednisolone dosing/ compliance                                     | x |   |  | x                                                                                                                                                                                                                                                             | x | x | x | x | x | x | x               |   | x | x | x |
| CNI dosing (if taking at entry)                                     |   |   |  | x                                                                                                                                                                                                                                                             | x | x | x |   |   |   |                 |   |   |   |   |

1. Day 0 is commencement of steroid treatment: eligibility blood and urine test results can follow. However randomisation must be after eligibility is confirmed. Day 0 (screening) and eligibility visits will be combined wherever possible, but must occur within a 4 week period if assessments performed over multiple visits.
2. Timings of treatment phase visits based on when first prednisolone dose given (SPPR). Once remission is achieved, move to post remission follow up visits
3. Please refer to section 11.12 of protocol for participant final visit timing
4. 3 monthly post-remission visit starting 3 months after the week 12 post remission visit till trial close
5. Neutrophils, Lymphocytes.
6. Urea, creatinine, e-GFR and albumin.

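### Section 10.3.3 is weaker and narrower than 9.2 and the synopsis on live vaccines, and no text covers live non-viral vaccines after the last dose while B-cell depletion is still expected

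*Protocol*

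**What the plan says.** Protocol 9.2 lists, among the criteria that preclude inclusion, "Live vaccine administration in the four weeks prior to enrolment and while remaining on IMP treatment". The synopsis repeats this in the same words. It covers all live vaccines and is a bar.

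Protocol 10.3.3 deals with vaccines again: "The use of live viral vaccines during IMP treatment or while remaining B-cell depleted is not advised". For any vaccine required during the study it adds that "it is recommended these should be completed at least 4 weeks prior to commencing the next dose of IMP". That second clause does not except live vaccines.

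On the length of treatment, the synopsis gives "Main study phase: 26 weeks", and 10.1.6 agrees (26 weeks, plus or minus 2). On the length of depletion, 10.1.2 describes two 1 g doses two weeks apart as "inducing B cell depletion for 6-12 months", and 9.5.2 says "By 12 months after treatment, B cell counts have generally returned to normal". The scheduled haematology in 11.15 is "Neutrophils, Lymphocytes". The open-label table (11.16) lists the same two counts. Neither table includes a B-cell count.

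**The concern.** Two sections state a safety rule for the same exposure, and they differ in force (a bar against advice) and in scope (all live vaccines against live viral ones). After randomisation a site is more likely to consult the concomitant-therapy section than the eligibility list, so the weaker text may well be the one used.

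The second problem comes after the last dose. The 9.2 bar is tied to treatment and ends with it, while the depletion clause in 10.3.3 names only viral vaccines. A live non-viral vaccine then falls under no text, at a time when the protocol expects participants given rituximab to lack B cells.

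The third problem is that the advice on live viral vaccines ends when depletion ends, but 10.3.3 gives no period and the trial does not measure the state. Sites may then choose different dates. A B-cell count ordered locally to settle the question would tend to reveal the arm.

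What is at stake is the safety of participants given rituximab. The comparison of the arms is not affected.

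**Working it through.** There is no statistical figure to reproduce. The check sets the texts side by side and then works out the dates.

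| Period | 9.2 and synopsis, all live vaccines | 10.3.3, live viral | 10.3.3, live non-viral |
|---|---|---|---|
| On treatment, up to dose 3 | Barred | Advised against | Not named; the 4-week clause accepts any vaccine |
| After dose 3, while depleted | Bar has ended | Advised against, no period given | Not named; no next dose is due unless a placebo participant enters the open-label phase |

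Inputs: dose 1 within 4 weeks of Day 0, dose 2 two weeks later (minus 1 or plus 2 weeks), dose 3 at week 26 plus or minus 2 (all 10.1.7); depletion of 6-12 months (10.1.2). I take 6 months as 26 weeks and 12 months as 52 weeks.

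1. Date of dose 2: earliest 0 + 1 = week 1; latest 4 + 4 = week 8.
2. Latest date for a vaccine under the 4-week clause before dose 3: 24 - 4 = week 20 to 28 - 4 = week 24.
3. From steps 1 and 2, 10.3.3 leaves a window from dose 2 to about weeks 20-24 for any vaccine. All of it lies inside the treatment period in which 9.2 bars live vaccines. A live non-viral vaccine given there meets 10.3.3 and breaches 9.2.
4. End of depletion counted from dose 3: at 6 months, 26 + 26 = week 52 (50-54 with the dose window); at 12 months, 26 + 52 = week 78 (76-80).
5. From dose 3 to about weeks 52-78, no text covers live non-viral vaccines.
6. Participants who have not remitted by week 16 leave the trial without dose 3 (11.5.1). Their last dose was at weeks 1-8, so 12 months ends at 1 + 52 = week 53 to 8 + 52 = week 60, well after they have left.

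**The case against.** The strongest reply is that the two rules can be followed together. Section 9.2 is the stricter, and a site that obeys it also satisfies 10.3.3. Section 10.3.3 names no live vaccine as allowed, and medications are checked at clinic visits before each infusion prescription (11.15, footnote 11). Much supportive care in 10.3.3 is left to local practice, so advisory wording fits the section. The documents give no rate of live-vaccine use, so harm is not shown.

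Much of this stands. During treatment the fault is a conflict of wording and not an absent rule, and no number of affected participants can be claimed. But the medication check does not tell a site which text governs, and the reply does not touch the period after the last dose, when 9.2 no longer applies.

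A reader might also infer that the depletion clause cannot be applied at a blinded site. The documents do not support that. A site can treat every participant as depleted and take the 12 months from 9.5.2, and 10.4 allows emergency unblinding for a valid medical or safety reason. What remains is that 10.3.3 does not state the period and the trial does not measure the state.

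**Conclusion.** The point holds as a minor participant-safety conflict. On treatment, 10.3.3 is weaker and narrower than 9.2 and the synopsis. After dose 3, live non-viral vaccines are uncovered while depletion is expected, to about weeks 52-78 from Day 0. The advice on live viral vaccines has no stated end in 10.3.3. Endpoint, power and analysis are not affected.

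The dates assume that the 6-12 months in 10.1.2, given there for two 1 g doses in other diseases, also holds after the single third dose. The risk concerns only participants who received rituximab.

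Two larger readings should be resisted. A reader might take the 18 months in 9.2 as a third depletion time and so see a wider disagreement. That criterion reads "Previous rituximab within 18 months preceding Day 0 (SPPR), or 12 months if there is evidence of B cell return in peripheral lymphocyte subsets" and is a washout for eligibility; the two statements that do describe depletion are compatible, with 12 months as the usual upper limit. A reader might also count all follow-up from dose 3 to the 24-month visit as unprotected. By the protocol's own account depletion has generally ended by 12 months after treatment, and follow-up stops earlier for participants who relapse or do not remit.

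**What to change.** Replace the vaccine sentence in 10.3.3 with:

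*Live vaccines (viral or non-viral) must not be given during IMP treatment, or for at least 12 months after the last dose of IMP or OLP rituximab, in both arms, unless the participant has been unblinded to placebo and does not receive OLP rituximab. Non-live vaccines should be completed at least 4 weeks before the next dose of IMP.*

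Add a cross-reference to 10.3.3 in 9.2 and in the synopsis, and tell participants who leave at week 16 their own 12-month date. The 12-month period is already used in the protocol for safety reporting after the last dose (9.5.2) and for contraception (12.1). A fixed minimum applied in both arms needs no B-cell test under blind.

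The cost is one replaced passage and two cross-references in a routine amendment, plus a memo to sites. No test, visit, CRF field or dosing rule changes. The downside is a longer live-vaccine restriction for placebo participants who stay blinded.
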